## Abstract

**Background:**

Approximately 900 children/adolescents are treated with radiotherapy (RT) every year in France. However, among the 80% of survivors, the cumulative incidence of long-term morbidity – including second malignancies - reach 73.4% thirty years after the cancer diagnosis. Identifying a priori the subjects at risk for RT sequelae is a major challenge of paediatric oncology. Individual radiosensitivity (IRS) of children/adolescents is unknown at this time, probably with large variability depending on the age when considering the changes in metabolic functions throughout growth. We previously retrospectively showed that unrepaired DNA double strand breaks (DSB) as well a delay in the nucleoshuttling of the pATM protein were common features to patients with RT toxicity. We aim to validate a high performance functional assay for IRS prospectively.

**Methods/design:**

ARPEGE is a prospective open-label, non-randomized multicentre cohort study. We will prospectively recruit 222 children/adolescents who require RT as part of their routine care and follow them during 15 years. Prior RT we will collect blood and skin samples to raise a primary dermal fibroblast line to carry out in blind the IRS assay. As a primary objective, we will determine its discriminating ability to predict the occurrence of unusual early skin, mucous or hematological toxicity. The primary endpoint is the measurement of residual double-strand breaks 24 h after ex vivo radiation assessed with indirect immunofluorescence (γH2AX marker). Secondary endpoints include the determination of pATM foci at 10 min and 1 h (pATM marker) and micronuclei at 24 h. In parallel toxicity including second malignancies will be reported according to NCI-CTCAE v4.0 reference scale three months of the completion of RT then periodically during 15 years. Confusion factors such as irradiated volume, skin phototype, previous chemotherapy regimen, smoking, comorbities (diabetes, immunodeficiency, chronic inflammatory disease...) will be reported.

**Discussion:**

ARPEGE would be the first study to document the distribution of IRS in the pediatric subpopulation. Screening hypersensitive patients would be a major step forward in the management of cancers, opening a way to personalized pediatric oncology.

**Trial registration:**

ID-RCB number: 2015-A00975–44, ClinicalTrials.gov Identifier: NCT02827552 Registered 7/6/2016.

## Background

2400 children and adolescents are newly diagnosed with cancer every year in France with an average age at diagnosis of 5 years [1, 2]. Although most protocols are currently attempting to limit the use of radiotherapy (RT) in this population, ionizing radiations remain a keystone in the management of approximately 900 patients who suffer from brain tumors, Hodgkin’s lymphoma, leukemia, soft tissues sarcomas, neuroblastomas, nephroblastomas or retinoblastomas [3].

However, among the 80% of survivors, the cumulative incidence of long-term morbidity – including second malignancies - reach 73.4% thirty years after the cancer diagnosis, with a cumulative incidence of 42.4% for severe, disabling, or life-threatening toxicities or specific death [4]. A major socio-economic impact is noticed (schooling issues, parental mobilization, unemployment, hospitalization, expensive symptomatic treatment, impoverishment, etc.). As 5–10% of adults treated with RT experience overreactions [5, 6], the distribution of individual radiosensitivity (IRS) in the pediatric population has never been described, with probably large age-related variability when considering all changes in metabolic functions throughout growth and tumor predispositions involving DNA repair pathways [7]. Only short series have been reported [8, 9]. Identifying those patients prior treatment would therefore have sound positive clinical implications such as the perspective of personalized therapy.

Predictive assays of RT toxicity are subject to a lack of universality, reproducibility and specificity, and are time consuming [10] so that there is no gold standard. An Increasing number of studies show that double-strand breaks (DSB) are the DNA damage most closely correlated with cell lethality and *in fine* toxicity if not repaired on the one hand, or genomic instability and cancer risk if misrepaired on the other hand [11, 12].

From 2003, the INSERM UMR1052 radiobiology group has elaborated a collection of primary skin fibroblast lines from patients (the majority of adults) with DNA repair deficiencies or who experienced RT toxicity on various tissues, with various severity and different post RT free intervals. The RT-induced distribution of candidate DSB recognition and repair proteins was measured with an indirect immunofluorescence (IIF) assay [13, 14] leading to a general classification of Human IRS based on the rate of unrepaired DSB 24 h after ex vivo irradiation (γH2AX marker). This last study showed further that a delay in the nucleoshuttling of the pATM protein, which is involved in the recognition of the DSB, was a common feature to patients with overreaction (OR) [15]. The maximal number of pATM foci between 10 min and 1 h post irradiation (pATM_max_) was found to be the parameter with the best correlation with each OR severity grade, independently of tumor localization and of the early or late nature of reactions. When taken as a binary predictive assay with the optimal cut-off value of 35 pATM foci, pATM_max_ foci showed promising predictive performances on a retrospective study, with an AUC of 0.97, a PPV of 99%, a specificity of 92% and a sensitivity of 100% [16].

We designed a prospective open-label, non-randomized multicenter cohort study to address the distribution of IRS and validate the performance of the IRS assay in the pediatric subpopulation. We will prospectively recruit 222 children/adolescents who require RT as part of their care path and follow them during 15 years to describe the specific morbidity including second malignancies. Prior RT we will collect blood and skin samples to raise a primary dermal fibroblast line to carry out the IRS assay – the result of which will have no impact on the RT prescription.

## Methods/design

### Aim, design and setting

#### Objectives

ARPEGE aims to explore the distribution of IRS in the pediatric population and to determine prospectively the discriminating ability of an IRS assay to predict the occurrence of early cutaneous, mucosal or hematological RT toxicity qualified as unusual in children/adolescents treated with RT for cancer.

The short term secondary objectives consist in: 1) identifying thresholds for each biomarker to predict the occurrence of unusual early toxicity in order to define IRS groups, 2) comparing the discriminating ability of IIF biomarkers (pATM and γH2AX on the one hand and micronuclei on the other hand), 3) developing a multivariate predictive model combining biomarkers.

The long-term secondary objectives consist in: 1) identifying the discriminating ability of biomarkers to predict the occurrence of Grade 3–4 late toxicities, and thresholds for each biomarker, 2) describing IRS biomarkers in the subset of patients developing secondary malignancies, 3) investigating the correlation between the severity of early toxicity and the occurrence of late toxicity (including secondary malignancies).

#### Endpoints

The primary endpoint is the skin fibroblast radiosensitivity defined as the residual DSB 24 h after ex vivo radiation assessed with IIF (γH2AX marker). Unusual early cutaneous, mucosal or hematological toxicity occurs within 3 months after RT and is defined by any of the following features appreciated with CTCAE v4.0 morbidity scale:Grade 2 or higher occurring at low doses (first week of treatment) orGrade 3–4 for more than 4 weeks after completion of RT and / or requiring surgery [17].

The discriminating ability of this biomarker to predict the occurrence of early toxicity will be assessed by the area under the receiver operating characteristic (ROC) curve.

Kinetic data on other DSB repair proteins are collected in order to refine the classification of IRS as secondary endpoints. The other biomarkers studied are therefore: 1) the number of pATM foci 10 min and 1 h post irradiation, 2) the average number of micronuclei per cell 24 h after irradiation (control IRS assay).

Late toxicity including second malignancies occurs at least 3 months after the completion of RT. Severe sequelae are defined by any grade 3–4 adverse effect with a progression lasting more than 90 days [17].

### Participants and recruitment

#### Inclusion/non-inclusion criteria

All children and adolescents treated with a curative intent in pediatric oncology and radiotherapy departments of the Grand-Est and Burgundy-Franche-Comté regions, France participating in the GE-HOPE network (i.e. Nancy, Reims, Dijon, Strasbourg and Besançon) as well as Lyon and Toulouse may be included according to the following inclusion criteria: 1) age < 18 years, 2) indication of RT as part of the local control strategy on the primary tumor, 3) standard fractionation (1.8–2.2 Gy/fraction, 5 sessions/week) irrespective of the technique and particle used, 4) patient affiliated to social security insurance, 5) patient and / or holder(s) of parental authority signed a written informed consent.

Exclusion criteria are: 1) contra-indication to skin biopsy, 2) contra-indication to RT, 3) RT in a palliative intent, 4) Previous irradiation in the same anatomic site (re-irradiation), 5) hypofractionation, 6) Impossible follow-up, 7) Persons deprived of liberty or under supervision.

### Recruitment

The participation to ARPEGE will be proposed as soon as the indication of RT is collegially validated in the care path of the patient. Three modalities of inclusion are permitted independently of surgery when required (Fig. 1):about 20% of patients could benefit from RT only if the response to neoadjuvant CT in unsatisfactory. This data is known late. The biopsy would therefore be sampled just before the RT (modality A, mainly lymphomas)60% of patients could benefit from neoadjuvant CT before RT (modality B, sarcomas, neuroblastomas, nephroblastomas, medulloblastomas…)20% of patients could benefit from definitive RT not preceded by CT (modality C, mainly brain tumors)

**Fig. 1 Fig1:**
[figure not shown]
Recruitment modalities and timing of the biopsy. CT: chemotherapy, RT: radiotherapy, Δ: biopsy. • Population A: definitive RT only if the response to neoadjuvant CT in unsatisfactory. • Population B: neoadjuvant CT before RT, eventually followed with CT. • Population C: definitive RT not preceded by CT

In the latter two cases, the biopsy will be anticipated.

### Data collection methods

All patients providing written informed consent to participate in the study are asked to complete a medical history. Clinical data that will be obtained in the ARPEGE study include patient-related data (age, height, weight, phototype, concurrent medications), cancer-related data (histology, topography), biopsy-related data (date, anesthesia modality, complications), treatment-related data (surgical procedure and related complications, chemotherapy regimen and related toxicity, radiotherapy characteristics: particle, energy, technique, fractionation, overall duration, target volume(s)). Comorbities that can affect IRS (e.g. diabetes, immunodeficiency, chronic inflammatory disease...) will be reported.

The following biological data from the radiobiological experiments will be reported in triplicates: γH2AX foci/nucleus prior irradiation and 24 h after, pATM foci foci/nucleus prior irradiation, 10 min and 1 h after, micronuclei/cell prior irradiation and 24 h after. 50 nuclei are counted for each condition.

Adverse events related to investigations (blood sample, skin biopsy or RT) as well as outcome will be recorded at RT simulation time, weekly during RT, at three months after RT, yearly during 5 years and every two years during the last 10 years (Table 1).

**Table 1 Tab1:** Chronogram and investigations of the ARPEGE study

	Inclusion	Weekly follow-up during RT							3 months after RT	Once/year during the 5 first years	Every 2 years during the 10 next first		End of study (15 years)
Written Informed consent signature	X												
Checking of inclusion and non-inclusion criteria	X												
Inclusion	X												
Clinical exam	X	X	X	X	X	X	X	X	X	X	X	X	X
Medical history	X												
Biopsy	X												
Blood sample	X												
Toxicity recording		X	X	X	X	X	X	X	X	X	X	X	X
Biopsy-related adverse events recording		X	X	X	X	X	X	X	X	X	X	X	X
Blood sample-related adverse events recording		X	X	X	X	X	X	X	X	X	X	X	X
Concurrent treatments recording	X	X	X	X	X	X	X	X	X	X	X	X	X

### Anticipated completion of enrollment

All patients should be included over a 30-month period. The duration of follow-up is 3 months after the completion of the RT for the main objective and 15 years for the secondary objectives. The overall duration of the study is therefore 17.5 years.

Our current expectation is that the final patient will be enrolled by July 2019, and the entire study will be completed by July 2033. Cumulative enrollment reached 10 cases as of August 2017.

### Intervention

#### Biopsy

After information and written consent from the holder(s) of parental authority and/or the child/adolescent, a 2–5 mm skin biopsy will be sampled under general anesthesia (provided for another purpose, e.g. bone marrow biopsy, lumbar puncture, central venous catheter…) or local anesthesia once the indication of RT is certain. In populations B and C, whenever there is a definite indication of postoperative RT known at the time of surgery, the biopsy may be collected from the operative specimen or at the scar level without modifying the nature or extent of the procedure. In other cases, a 2 mm (12 G) punch biopsy will be sampled at the buttock. The biopsy aims to collect the epidermis and superficial dermis without ever coming into contact with the superficial muscular fascia. The use of iodized antiseptics is prohibited. The anonymized specimen will be sent fresh in 10 mL of appropriate culture medium at ambient temperature and within 48 h.

In parallel, 2.5 mL of venous blood may be collected to enrich a biological collection that will allow for further radiobiological studies (optional).

### Cell culture and irradiation

Patient-specific non-transformed fibroblast primo cultures will be raised. The cell lines will be irradiated (2 Gy) at early passage in the plateau phase of growth to mimic healthy tissues and to avoid any artifacts resulting from the cell cycle. The irradiated and control cells will be fixed at strategic times (10 min, 1 h, and 24 h).

### Immunofluorescence assay

Protocols for immunofluorescence with antibodies against pATM and γH2AX proteins and with DAPI counterstaining for scoring micronuclei have been described previously [15, 18]. The procedures will be repeated in triplicates and three independent experts from two centers will count the foci in blind to get a kinetic for each marker and classify each patient according to his/her IRS, which will remain hidden from the oncologist.

### Radiotherapy

RT will be planned according to state of the art recommendations without any individual adaptation. The dose delivered to the organs at risk will be systematically collected on the dose-volume histograms.

### Toxicity data collection

Early toxicity will be reported once a week during RT and then at 3 months, and rated on the NCI-CTACE v4.0 scale. Late toxicities, including second cancers, will be collected over 15 years and rated according to the same scale.

### Statistical analysis

#### Statistical methods

The discriminating ability of any IIF biomarker to predict the severity of toxicity will be defined by the area under the ROC (AUC) curve as well as its 95% confidence interval. The following hypothesis: H_0_: AUC ≤ 0.7 against H_1_: AUC > 0.7 will be tested.

The discriminating capacity of biomarkers will be compared by the nonparametric Mann-Whitney approach [19]. For each biomarker, the choice of the optimal threshold will be determined using the Youden index to maximize both sensitivity and specificity. The sensitivity and specificity of each biomarker will be compared by a Mac Nemar test. A multivariate logistic regression will be carried out on all biomarkers with a level of significance less than 0.2 in bivariate analyses. The simplification of this model will be carried out by a logistic multivariate regression with a downward selection at significance level 0.2 [20] using the bootstrap re-sampling method [21]. The discriminating capacity of the model will be estimated using the area under the ROC curve (95% confidence interval). The correlation between early and late toxicity will be evaluated with a Chi-Squared or Exact Fisher test.

The analysis of the main and secondary short-term objectives is planned as soon as all the included patients have 3 months of follow-up. Intermediate analysis of the long-term secondary objectives will be carried out at 2, 5 and 10 years.

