### Power calculation

If we hypothesize an area under the ROC curve of 0.85 for the main endpoint, a 15% occurrence of early toxicity [22] and a risk of first specie at 2.5% then 222 patients are necessary to obtain a power greater than 0.8 including 10% of lost to follow-up. Thirty unusual early and late toxicities are therefore expected.

According to inter-regional data updated in 2015, the inclusion potential would be 150 patients per year in the territory.

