## Discussion

From the basic research carried out by INSERM UMR1052 radiobiology group, Neolys Diagnostics proposes a powerful decision-making tool to the radiation oncology community in order to reduce side effects, while optimizing the treatment efficiency. With quasi optimal positive and negative predictive values, it is the only IRS test able to accurately quantify this trait according to a continuous spectrum with a strong biologic rationale when compared with other IRS assays. ARPEGE represents a unique opportunity to validate the skin IRS assay according to an appropriate methodology. To our knowledge, we lead the first study to document the specific distribution of IRS in the pediatric population.

The application on the pediatric population is relevant due to the scarcity of cancer prevalence and indications of RT, the specific tissue homeostasis in this population, and the major societal challenges of optimizing the quality of survival of children who will recover.

Due to the multiplicity of clinical situations in this heterogeneous population and in particular the protocols of concurrent chemotherapy we had considered to harvest the cells in the presence of drugs before irradiating them - in order to evaluate their radiosensitization potential. We abandoned this idea because of the over-cost, low feasibility and reproducibility, and bias on the constitutional trait pointed out by the assay.

With regard to the documents intended for children and their decision-making autonomy, it appeared necessary to cover all the differences in development. Using appropriate language and information materials, we always seek the agreement of the child. For this study, we developed 4 different information materials and consent forms for parents and children aged 13–17, 8–12 and under 8 years of age. A Childhood Cancer Parents Association validated the materials.

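### Every cut-off is chosen by Youden on the study's own data with no stated optimism correction, and the published 35-foci pATM rule has no pre-specified test

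*Protocol article*

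**What the plan says.** The Background sets the aim: to "address the distribution of IRS and validate the performance of the IRS assay in the pediatric subpopulation". The paragraph before it reports the only decision rule with a numerical cut-off in the article. It is based on pATMmax, the maximal pATM foci count between 10 min and 1 h after irradiation, described as the parameter that correlates best with the severity of overreaction. "When taken as a binary predictive assay with the optimal cut-off value of 35 pATM foci", it had an AUC of 0.97, PPV 99%, specificity 92% and sensitivity 100% in a retrospective study.

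Under Endpoints, the primary marker is residual γH2AX foci at 24 h. The pATM marker is secondary and listed as "the number of pATM foci 10 min and 1 h post irradiation"; pATMmax is not named.

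Under Objectives, identifying a threshold for each biomarker is a short-term secondary objective. Statistical methods carries this out: "For each biomarker, the choice of the optimal threshold will be determined using the Youden index to maximize both sensitivity and specificity". A McNemar test then compares sensitivity and specificity between biomarkers. Bootstrap resampling is mentioned only for simplifying the multivariate model.

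The primary hypothesis uses no cut-off: "AUC ≤ 0.7 against H_1_: AUC > 0.7 will be tested". The Discussion describes the assay as a decision tool: "With quasi optimal positive and negative predictive values".

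**The concern.** Validating a binary test means taking a rule fixed beforehand and counting its errors in new patients. Choosing the cut-off that maximises sensitivity plus specificity in a cohort, then reporting both from that cohort, is derivation, and the reported figures are biased upwards. The article chooses the second procedure for each biomarker, including the one that already has a published cut-off.

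Two things are at stake. First, the sensitivities and specificities from the short-term analysis will be optimistic. The McNemar comparison inherits this, and unevenly, because a weaker marker gains more from the search. Second, the published rule would get no pre-specified estimate of its error rates in children, although the article foresees later dose-adaptation trials that use individual radiosensitivity in advance. Such trials need the error rates of a fixed rule at a natural event rate.

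**Working it through.** **1. The plan's own sample size, to fix the event count.** Inputs from Statistical methods and Power calculation: null AUC 0.7, alternative 0.85 ("If we hypothesize an area under the ROC curve of 0.85 for the main endpoint"), "a 15% occurrence of early toxicity", type I error 2.5% (one-sided, from the stated hypotheses), power above 0.8, 10% lost.

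Evaluable patients: 222 × 0.9 = 199.8, about 200. Events: 200 × 0.15 = 30. Non-events: 170.

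Hanley–McNeil variance: [A(1−A) + (n₁−1)(Q₁−A²) + (n₀−1)(Q₂−A²)]/(n₁n₀), with Q₁ = A/(2−A), Q₂ = 2A²/(1+A), n₁ = 30, n₀ = 170.

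- A = 0.70: (0.210 + 1.405 + 14.613)/5100 = 0.00318, SE 0.0564.
- A = 0.85: (0.128 + 0.482 + 9.900)/5100 = 0.00206, SE 0.0454.
- Power = Φ[(0.15 − 1.96 × 0.0564)/0.0454] = Φ(0.87) = 0.81.

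Solving for 80% power gives 197 evaluable (219 enrolled) with this variance, or 198 (220 enrolled) with the Obuchowski binormal variance. So 222 reproduces, and the primary test has the power claimed.

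**2. Optimism of same-sample Youden cut-offs.** Assumptions: non-events N(0,1), events N(d,1), d = √2·Φ⁻¹(AUC); 30 events, 170 non-events; 4,000 simulated cohorts per AUC. In each cohort the Youden cut-off is chosen and scored on that cohort, then its true sensitivity and specificity are computed from the known distributions.

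| True AUC | Sensitivity: apparent / true | Specificity: apparent / true | Youden index: apparent / true | Overstatement: sensitivity, Youden |
|---|---|---|---|---|
| 0.70 | 0.701 / 0.618 | 0.663 / 0.651 | 0.364 / 0.269 | 0.083, 0.096 |
| 0.85 | 0.812 / 0.745 | 0.781 / 0.773 | 0.593 / 0.518 | 0.066, 0.075 |
| 0.97 | 0.936 / 0.886 | 0.918 / 0.913 | 0.853 / 0.800 | 0.049, 0.054 |

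(Overstatements were taken before rounding, so the last digit can differ by one.) Nearly all the bias falls on sensitivity, because the events are few. At AUC 0.85 the chosen cut-off has a 95% range of about 0.22 to 1.36 marker SD, against a true optimum of d/2 = 0.73. The gap in Youden index between a 0.97 and a 0.70 marker is truly 0.800 − 0.269 = 0.531 but appears as 0.853 − 0.364 = 0.489, so the comparison favours the weaker marker.

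**3. Whether the retrospective PPV can carry over.** PPV = Se·p/[Se·p + (1−Sp)(1−p)], with Se = 1 and Sp = 0.92 from the Background.

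- Event share that gives PPV 0.99: p = 0.99 × 0.08/(0.99 × 0.08 + 0.01) = 0.0792/0.0892 = 0.89.
- At the planned p = 0.15: 0.15/(0.15 + 0.08 × 0.85) = 0.15/0.218 = 0.69.
- At the 5–10% overreaction rate the Background quotes for adults: 0.05/0.126 = 0.40 and 0.10/0.172 = 0.58. These are context only; they concern another population.

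So PPV falls from 99% to about 69% through the event rate alone, even if sensitivity and specificity transfer perfectly.

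**4. What a fixed rule would deliver at the planned size (Clopper–Pearson 95% intervals).** Sensitivity 30/30: 88.4 to 100%. Sensitivity 27/30: 73.5 to 97.9%. Specificity 156/170 (92%): 86.6 to 95.4%. A fixed cut-off carries no selection optimism, and no change in sample size is needed.

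**The case against.** The strongest reply is that the confirmatory analysis uses no cut-off. Marker, outcome and null value are fixed in advance, foci are counted blind, and 222 patients are enough. That is a real prospective test of discrimination, and an AUC with its interval is planned for any immunofluorescence marker. This stands in full. A reader might infer from the Youden sentence that the study cannot validate the assay at all; the article does not support that, because thresholds play no part in the primary test.

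Next, deriving thresholds is openly declared, and there are grounds for it: the earlier collection came mostly from adults, and the article expects radiosensitivity to vary with age. The 35-foci value was the optimum in one retrospective series covering early and late reactions, and the article never names it as the rule under test for unusual early toxicity. This also stands. It justifies estimating paediatric thresholds, but not leaving the existing rule without a planned test or reporting the new thresholds uncorrected.

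Third, the 10 min and 1 h counts are collected for everyone, so the 35-foci rule could be applied at any time. A reader might infer that the question becomes unanswerable; it does not. What is lost is pre-specification.

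Finally, a derived variable, a list of predictive values and interval methods are commonly left to an analysis plan, so their absence from an article is no error. Agreed. The point rests on the method the article does state, for each biomarker, and on its mismatch with the validation aim.

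**Conclusion.** The point holds in a limited form. The γH2AX AUC test and its sample size are unaffected. The threshold analysis as stated will give optimistic sensitivity and specificity: about 5 to 8 points on sensitivity and 0.05 to 0.10 on the Youden index. This rests on equal-variance binormal markers, 30 events and 170 non-events, and true AUCs from 0.97 to 0.70; skewed foci counts or fewer events would change the figures. It also assumes that no optimism correction for cut-offs is set out in an analysis plan not seen here.

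The published binary rule has no pre-specified test in a study presented as validation. The PPV arithmetic does not reveal an error in any planned analysis; it shows why the retrospective 99% cannot stand in for a test in this cohort. This should be fixed, but it does not endanger the primary conclusion.

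**What to change.** Before outcomes are examined, amend the protocol or analysis plan as follows.

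1. Define pATMmax as the larger of the 10 min and 1 h counts, and write out the 35-foci rule, including which side of the cut-off counts as test-positive.
2. Pre-specify a secondary analysis of that rule against unusual early toxicity: sensitivity, specificity, PPV and NPV at the cohort's own event rate, with exact 95% confidence intervals.
3. Label the Youden thresholds exploratory. Report their sensitivity and specificity with bootstrap or cross-validated optimism correction, repeating the cut-off search in each resample, and read the McNemar comparison in the same light.
4. Quote predictive values only with the event rate at which they hold, and do not carry the retrospective 99% over to this population.

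The cost is wording and a little programming; the counts are already collected and the sample size stays at 222. The downside is that less favourable figures will have to be stated. Timing matters: a rule named after the outcomes are known is no longer pre-specified.

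### McNemar tests at each biomarker's own in-sample Youden cut-off would flag a difference, nearly always in specificity, in about half of trials with equally discriminating biomarkers

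*Protocol article*

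**What the plan says.** All references are to the protocol article.

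- **Objectives.** Short-term secondary objective 1 is "identifying thresholds for each biomarker to predict the occurrence of unusual early toxicity in order to define IRS groups". The cut-offs are therefore found in this cohort. Objective 2 compares the discriminating ability of pATM and γH2AX with that of micronuclei.
- **Statistical methods, cut-off rule.** "For each biomarker, the choice of the optimal threshold will be determined using the Youden index to maximize both sensitivity and specificity".
- **Statistical methods, next sentence.** "The sensitivity and specificity of each biomarker will be compared by a Mac Nemar test".
- **Statistical methods, cut-off-free comparison.** "The discriminating capacity of biomarkers will be compared by the nonparametric Mann-Whitney approach [19"]. This compares AUCs and comes just before the cut-off rule.

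No validation sample, prespecified cut-off or allowance for estimating the cut-off is attached to the McNemar tests. The bootstrap appears only for simplifying the logistic model. The Background reports a retrospective result "with the optimal cut-off value of 35 pATM foci", but nothing links that value to these tests.

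**The concern.** McNemar's test asks whether two binary tests, applied to the same patients, have the same sensitivity (among events) or the same specificity (among non-events). Its error rate assumes that the rule turning each biomarker into a binary test was set without looking at those patients.

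Here each rule is tuned on them. The Youden sum is nearly flat around its maximum, so chance decides where on the curve each marker is cut. Two markers with the same ROC curve can easily be cut at different points, one more specific and the other more sensitive. McNemar then reports a difference.

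What is at stake is the comparison of the immunofluorescence markers with micronuclei, which the Endpoints section calls the control assay. A significant McNemar result could be reported as one assay outperforming the other when their discrimination is equal. The plan does not say which result takes precedence if McNemar and the AUC comparison disagree.

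**Working it through.** **1. Inputs.** From Power calculation: AUC 0.85, 15% early toxicity, first-kind error 2.5%, power above 0.8, 222 patients including 10% lost, 30 toxicities. From Statistical methods: null AUC 0.70. Assumed, because the article does not give them: a two-sided 5% level for McNemar, binormal markers with equal true AUC and equal true optimal cut-off, and within-patient correlation 0 to 0.9.

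**2. The plan's own figure.** Evaluable patients: 222 × 0.9 ≈ 200. Events: 0.15 × 200 = 30, leaving 170 non-events. The Hanley–McNeil standard errors at 30/170 are 0.0564 (AUC 0.70) and 0.0454 (AUC 0.85). One-sided power at 2.5% is Φ[(0.15 − 1.96 × 0.0564)/0.0454] = Φ(0.87) ≈ 0.81. The sample size reproduces, and 30/170 is the right setting for the check.

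**3. Why the cut-off wanders.** For a binormal marker the mean shift is √2·Φ⁻¹(0.85) = 1.466. At cut-off c, specificity is Φ(c), sensitivity is Φ(1.466 − c), and J = sensitivity + specificity − 1.

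| Specificity | c | Sensitivity | J |
|---|---|---|---|
| 0.62 | 0.305 | 0.877 | 0.497 |
| 0.768 (true optimum) | 0.733 | 0.768 | 0.536 |
| 0.91 | 1.341 | 0.550 | 0.460 |

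Over 29 points of specificity, J falls below its maximum by no more than 0.536 − 0.460 = 0.076. The standard error of a sensitivity of 0.768 in 30 events is √(0.768 × 0.232/30) = 0.077. The data can barely tell these cut-offs apart. In simulation the realised Youden specificity of one marker did run from about 62% to 91% (5th to 95th percentile).

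**4. Rejection rates for two equal markers.** 2,000 replicates per setting, 30/170, AUC 0.85, exact McNemar, two-sided 5%. The Monte Carlo standard error near 50% is √(0.25/2000), about 1.1 points.

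| Cut-off | Correlation | Sensitivity test | Specificity test | Either |
|---|---|---|---|---|
| Youden | 0 | 8.2% | 46.9% | 48.2% |
| Youden | 0.3 | 7.8% | 47.4% | 48.2% |
| Youden | 0.5 | 9.6% | 47.2% | 48.6% |
| Youden | 0.7 | 11.2% | 55.0% | 55.7% |
| Youden | 0.9 | 9.6% | 58.0% | 58.0% |
| Fixed in advance | 0 | 2.8% | 4.1% | 6.7% |
| Fixed in advance | 0.5 | 2.1% | 3.4% | 5.6% |
| Fixed in advance | 0.7 | 2.2% | 3.4% | 5.6% |

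With fixed cut-offs at AUC 0.70 as well as 0.85, the rates are 1–4% (sensitivity) and 3–4% (specificity).

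**5. Sensitivity of the result.** Share with at least one significant test:

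- By true AUC, correlation 0 to 0.9: 60–68% at 0.70, 52–61% at 0.80, 48–58% at 0.85, 42–51% at 0.90, 32–42% at 0.95, 27–36% at 0.97.
- Uncorrected instead of exact McNemar, AUC 0.85: 52–62%.
- Level halved to 2.5% per test, AUC 0.85: 42–53%.
- All 222 evaluable (33/189), AUC 0.85, correlation 0 to 0.7: 47–56%.
- Five times the sample (150/850), AUC 0.85, correlation 0 to 0.7: 62–70%. The two cut-offs draw closer, but more slowly than the test gains precision.

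**6. What the significant results look like.** At AUC 0.85 and correlation 0.3 to 0.7, about 85–89% of them show sensitivity and specificity differing in opposite directions, as expected from two points on one curve.

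**7. The cut-off-free alternative.** A paired AUC comparison (DeLong) of the same equal markers at AUC 0.85 rejects in 4.5–5.8%.

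**The case against.** **Objective 2 already has a valid test.** It asks about discriminating ability, which the article measures by the area under the ROC curve, and the planned nonparametric comparison addresses exactly that. McNemar is listed separately and is not named as the test for objective 2. This stands. A reader might infer that the objective would be decided by threshold noise, or that the primary result is at risk. The documents support neither inference.

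**Equal discrimination is not McNemar's null hypothesis.** Two identical markers cut at different points do differ in specificity at those cut-offs, so much of the excess is a real difference between the chosen points. This also stands, and it fits the higher rate in larger samples. It narrows the point but does not remove it: the difference belongs to the cut-offs that this sample happened to give, and it says nothing about which biomarker discriminates better.

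**A reader would see the trade-off.** Often, but not reliably. With 30 events the opposing shift in sensitivity is frequently not significant, so a significant specificity result can stand alone.

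**The details may sit in the full protocol or analysis plan.** They may. But the article itself states both the cut-off rule and the test, in consecutive sentences, and an analysis plan that follows them inherits the problem.

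**Conclusion.** The point holds in a limited form and should be fixed. At the planning values, with correlation 0.3 to 0.7, two equally discriminating biomarkers give a significant specificity test in about 47–55% of trials and a significant sensitivity test in about 8–11%. At least one is significant in about half.

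It would be wrong to say that each test errs half of the time: the excess is almost all in specificity. Nor is about half a universal figure. At AUC 0.97, the retrospective value that the Background reports for pATM, the share is 27–36%; at the null AUC of 0.70 it is 60–68%. Nor are the 30 events alone to blame, since a larger sample does not lower the rate.

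The figures rest on the assumed 5% level, binormal shape, correlations and equal true cut-offs. Inflation was well above 5% in every setting examined. The primary AUC test, the sample size and the planned paired AUC comparison are not affected.

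**What to change.** 1. State that the paired nonparametric AUC comparison already planned in Statistical methods is the sole inferential test for short-term secondary objective 2.
2. Report sensitivity and specificity at the Youden cut-offs descriptively, without McNemar p-values.
3. If sensitivities are to be tested, compare them at a common prespecified specificity, using a paired bootstrap that re-derives the cut-offs in every resample.
4. Keep McNemar only for comparisons in which every cut-off was fixed before the data. Setting pATM at the published 35 foci while taking the other marker's cut-off from the cohort would not qualify. The article quotes no such published value for γH2AX or micronuclei.

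Cost: wording in the protocol and analysis plan, one bootstrap routine if item 3 is used, and the loss of McNemar p-values at the Youden cut-offs. No extra patients or data are needed.
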